## Rationale and Objectives

In recent years there has been a novel approach for the treatment of chronic pain: Floatation REST (restricted environmental stimulation therapy). Floating is a therapeutic approach developed in the 1950s [6, 7] which patients float in a specialized pool or tank on water that contains high concentrations of Epsom salt (Magnesium sulfate). Water is kept at skin temperature (35-36°C) and the pool or tank is shielded to provide almost complete darkness and silence. This therapeutic approach has proven to be effective in alleviating chronic pain [2].

While the high salinity of the water allows effortless floating and thus leads to muscle relaxation, the dark and silent environment without somatosensory stimulation greatly reduces sensory input. Thus, the two main mechanisms through which floatation REST may influence pain are the floatation itself and the sensory deprivation.

Due to the difficulties associated with designing a credible placebo control there have been no randomized controlled trials (RCTs) with patients blinding so far. Such blinding, however, is crucial, as the futuristic design of the pools / tanks and the unusual form of intervention are prone to elicit large placebo effects.

Here, we plan to conduct the first patient blinded RCT with a credible placebo control for floating and a no-treatment group.

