## Study Design

To investigate the therapeutic effects of floating and sensory deprivation on chronic pain we will divide the participants into three groups using a central randomization procedure.

- The **intervention group** will have the full floating experience: high buoyancy and maximal sensory deprivation.
- The **control group** will have a minimal floating experience designed as a placebo control. To achieve this we will manipulate the two mechanisms mentioned above: the water will have reduced buoyancy (low salinity) and there will be visual, auditory and somatosensory stimuli to reduce sensory deprivation to a minimum.
- The **no-treatment group** will be a waiting-list control. Patients in this group will not receive any treatment.

Our study will investigate short- and long-term effects of floating by evaluating separate endpoints after each floating session and after completion of the study (i.e. after five floating sessions).

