## Endpoints

The study has **short-term endpoints** to assess the effect of each single floating session and **long-term endpoints** to assess the effect of a course of five successful floating sessions. While the former will be assessed before and after each floating session, the latter will be assessed one week after the final floating session and in two follow-ups at 12 and 24 weeks after completion. The only exception are pain area and widespreadness that will not be included in the follow-up assessments.

The study is successful, when the primary outcome shows significant differences between the intervention group and the control group at first assessment (one week after the final floating session).

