### Primary outcome (long-term):

The primary endpoint of the study is the reduction of pain (maximum and average) as measured by a numeric rating scale (NRS) retrospectively for one week.

**Secondary long-term outcomes** comprise improvements in

- 1.) Reduction of pain (maximum and average) by 30% or more (dichotomous)
- 2.) Pain-related disability (PDI)
- 3.) Trait Anxiety (STAI Trait)
- 4.) Depression (BDI)
- 5.) Quality of life (SF-12)
- 6.) Quality of sleep (NRS)
- 7.) Use of pain medication

**Secondary short-term outcomes** comprise improvements in

- 1.) Acute pain intensity (NRS)
- 2.) Acute pain area and widespreadness (from electronic pain drawing)
- 3.) State Anxiety (STAI State)
- 4.) Heart rate variability (improvement of sympatho-vagal balance indicated by an increase in HF- and a decrease in LF-HRV)
- 5.) Unusual bodily sensations during floating (electronic drawing)
- 6.) Altered states of consciousness during floating (5D-ASC)

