## Data analysis

All statistical analyses will be conducted using R (<https://www.r-project.org/>) and Python (<https://www.python.org/>). Pain and sensation drawings will be analysed with the FMRIB Software Library (<https://fsl.fmrib.ox.ac.uk/fsl/>).

The statistical test for the primary outcome will be a two-tailed two-sample t-test of the differences (before treatment - one week after treatment). In case of significant differences in the primary outcome measure at baseline, an ANCOVA model will be used instead. If the prerequisites for t-tests are not granted, we will use non-parametric tests to compare the differences. The study will be positive if we observe a significant difference ( $p < 0.05$ ) between the intervention and the control group.

For the secondary long-term outcomes we will use Chi-squared test (for the dichotomous condition) and mixed ANOVAs with between-subject factor "group" and within-subject factor "time" for the other outcomes. Secondary short-term outcomes will be assessed using two-tailed paired t-tests.

All outcomes will be assessed in an Intention-to-Treat (ITT) analysis under the following conditions:

- The subjects who drop out before the first session will be excluded from the analysis and replaced by other subjects.
- We will continue to acquire the endpoints, keeping the same time intervals, i.e. 1, 12 and 24 weeks after the last session.
- In the case that we cannot assess the endpoint due to missing data, the subject will be excluded from the analysis and replaced by another subject.

In order to test for the robustness of the therapeutic effect, we will also conduct per-protocol analyses afterwards.

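### The short-term outcomes are tested only before-versus-after within a group, so the plan cannot show that floating beats placebo floating, and two of the six outcomes have no pair to test

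*Combined protocol and SAP*

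**What the plan says.** All references are to the combined protocol and SAP.

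- **Aim.** Study Design states: "Our study will investigate short- and long-term effects of floating by evaluating separate endpoints after each floating session". Endpoints gives the short-term outcomes the task "to assess the effect of each single floating session".
- **Test.** Data analysis states: "Secondary short-term outcomes will be assessed using two-tailed paired t-tests". This covers all six short-term outcomes and names no group factor.
- **Other outcomes.** The same section is explicit about groups elsewhere. For pain one week after treatment, "The statistical test for the primary outcome will be a two-tailed two-sample t-test of the differences". Most long-term secondary outcomes get a mixed ANOVA with a group factor.
- **Control.** Rationale and Objectives warns that the tank and the unusual intervention "are prone to elicit large placebo effects". Study Design then sets up a placebo-floating arm.
- **Timing.** On the short-term outcomes, Endpoints says: "While the former will be assessed before and after each floating session". The section on study procedures lists outcomes 1 to 3 only before the float, heart rate variability (outcome 4) before and after, and outcomes 5 and 6 only after.
- **Outcomes 5 and 6.** Both are defined as experiences during the float: bodily sensations drawn electronically, and "Altered states of consciousness during floating (5D-ASC" scale).

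**The concern.** A paired t-test asks whether the mean change in one group differs from zero. It does not ask whether the change under floating exceeds the change under placebo floating. Expectation, or simply resting for a 90-minute session, could produce a real before-after change in both arms. The protocol itself expects a large placebo response and built a placebo arm to separate it from the effect of floating. The short-term tests do not use that arm.

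Two further gaps follow from the same sentence. For outcomes 5 and 6 no pre-float value can exist, so the stated test cannot be run as a before-after comparison. Each participant also contributes five sessions, and the plan does not say whether these are tested one by one, averaged or modelled together. That choice could be made after the data are seen.

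At stake is what may be claimed about the effect of single sessions, which is one of the trial's two stated aims.

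**Working it through.** **1. Can the paired test be a comparison between arms?** The sample size section says the groups will be balanced for age, gender and average pain intensity. It describes no individual matching. With no cross-arm pairs, the pairing must be within a participant. The no-treatment group has no floating sessions, so the relevant contrast is intervention against placebo floating. No section specifies it for the short-term outcomes.

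**2. Which outcomes have a pair?**

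| Outcome | Endpoints | Study procedures | Before-after pair? |
|---|---|---|---|
| 1–3 (acute pain, pain area and spread, state anxiety) | before and after | before only | only if Endpoints is followed |
| 4 (heart rate variability) | before and after | before and after | yes |
| 5–6 (sensations, altered states) | before and after | after only | no, by definition |

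**3. How often is the within-group test significant when floating adds nothing?** The plan gives no figure for the short-term tests, so there is none to reproduce.

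Inputs from the documents: n = 24 per arm and two-sided alpha 0.05, both from the sample size section. Assumption: the same true mean change in both arms, dz = mean change / SD of change, taken from 0.4 to 0.8. The documents give no SD for any short-term change.

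Paired test: noncentral t with 23 degrees of freedom and noncentrality dz × √24, where √24 = 4.899. Two-sample test of change: noncentrality (dz − dz) × √(24/2) = 0, so it rejects at its nominal 5%. A simulation of 100,000 trials was run at three of the values.

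| dz in both arms | dz × √24 | Floating arm's paired test significant | Two-sample test of change rejects |
|---|---|---|---|
| 0.4 | 1.96 | 46.7% | 5.1% (simulated) |
| 0.5 | 2.45 | 65.0% | 5% (theory) |
| 0.6 | 2.94 | 80.4% | 5.0% (simulated) |
| 0.8 | 3.92 | 96.3% | 4.9% (simulated) |

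The paired test is not faulty here: it correctly detects a change. The change says nothing about floating against placebo.

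**4. What could the between-arm test detect?** With 24 per arm and one change score per person, a two-sided two-sample t-test has 80% power at a between-arm d of about 0.83 and about 40% at d = 0.5. Averaging sessions may improve on this, by an amount that depends on a within-person correlation the documents do not give.

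**The case against.** The strongest defence is that these outcomes do not decide the trial. Endpoints and Data analysis both rest success on the primary outcome, intervention against control, one week after the last session, and that test is a two-sample test. This stands. A reader might infer that the trial's conclusion is compromised; the documents do not support that.

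Three other strong readings are tempting and also go too far.

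- **That a paired t-test cannot handle five sessions.** A separate test per session, or one test on each person's average, is valid for change within an arm (multiplicity aside). The wording in Study Design and Endpoints points towards session-level evaluation. Pooling 24 × 5 = 120 pairs as if independent would inflate the error rate: with an assumed within-person correlation of 0.3 or 0.5 the variance inflates by 1 + 4 × 0.3 = 2.2 or 1 + 4 × 0.5 = 3.0, and a nominal 5% test has a true size of about 19% or 26%. But the plan nowhere proposes such pooling. The gap is the missing rule.
- **That the plan will read significance in one arm only as an effect of floating.** It states no such rule. If someone applied it, significance in the floating arm alone would arise with probability p(1 − p). With p from the table in step 3, that is 25%, 23%, 16% and 3.5% of trials at dz = 0.4, 0.5, 0.6 and 0.8. This warns against misuse and depends strongly on the assumed effect.
- **That regression to the mean drives the before-after change.** Inclusion sets no minimum pain score, and pre-float values at scheduled visits are not selected for being high. The expected placebo response is the sound argument.

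Data analysis also says sensation drawings will be analysed with an imaging software library. That names a tool for outcome 5, but not a contrast between arms.

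**Conclusion.** The point holds. As written, the short-term analysis can show change within a group but not superiority of floating over placebo floating. Outcomes 5 and 6 have no before-after pair, and the handling of the five sessions is undefined. These three conclusions rest on the text alone.

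The 47% to 96% range illustrates how little a significant paired test says about floating. It assumes equal true change in both arms, 24 per arm, normally distributed changes and dz between 0.4 and 0.8. It is not a false-positive rate of any comparison the plan states.

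This should be fixed before any short-term claim about floating is made. It limits those claims and leaves the primary test untouched.

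**What to change.** Replace the paired t-tests with an intervention-minus-control contrast.

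- **Outcomes 1 to 4.** Fit a linear mixed model to the session change (post minus pre) with group, session, group-by-session and a random participant effect. Test the group contrast averaged over sessions. If a baseline covariate is used, take the pre-float value of session 1. Pre-float values from session 2 on are measured after randomisation and may carry effects of earlier floats. State that later-session contrasts are conditional on those earlier floats.
- **Outcome 6.** Use the post-float score in the same model.
- **Outcome 5.** Define a scalar from the drawing in advance, for example the area marked, and use its post-float value in the same model. Alternatively, specify a between-group image analysis.
- **Within-group changes.** Report them descriptively only.
- **Timing.** Reconcile Endpoints with the section on study procedures for outcomes 1 to 3, because the contrast needs their post-float values.

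The cost is SAP wording and a little more analysis work, plus presentation to the ethics committee as the Amendments section requires. No new data are needed if outcomes 1 to 3 are collected as Endpoints describes. Outcomes 4 to 6 already have the measurements they need.

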## Study assessments

- 1.) All pain scores will be acquired using numeric rating scales from 0 ("no pain") to 100 ("maximum imaginable pain"). Ratings will assess the period of one week before the day of assessment.
- 2.) Pain-related disability, state and trait anxiety, depression and quality of life will be assessed using the following validated questionnaires
  - a.) Pain disability index, PDI [9]
  - b.) State-Trait Anxiety Inventory, STAI [10]
  - c.) Beck Depression Inventory, BDI-II [1]
  - d.) 12-Item Short Form Survey, SF-12 [11]

All ratings will assess the period of one week before the day of assessment.

- 3.) Pain area and widespreadness (Widespread pain index, WPI) will be derived from electronic pain drawings acquired using the tablet PC application "SymptomMapper" developed by our group. Ratings will assess the period of four weeks before the day of assessment.
- 4.) HRV will be measured before and after each floating session using a Nilas MV Diagnostik- und Regulationssystem (Nilas MV GmbH, Hamburg).
- 5.) Unusual bodily sensations during floating will be acquired from electronic drawings with the "SymptomMapper" software.
- 6.) Altered states of consciousness will be assessed using the 5-Dimensional Altered States of Consciousness Rating Scale, 5D-ASC [4].
- 7.) Sleep quality will be assessed with a numeric rating scale. Patients will be asked how much their pain impairs their sleep on a scale from 0 ("not at all") to 100 ("very much").
- 8.) Use of pain medication will be assessed by patients' self report.
- 9.) To assess the treatment belief, subjects will receive the following written question "Which treatment do you believe you received?" and offered the replies "real floating", "placebo floating" or "uncertain".

- 10.) To assess credibility of and expectancy in the treatment, a four-item Borkovec and Nau's self-assessment scale will be used [3].

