## Study procedures on each study day

The subject recruitment will start in February 2018 according to the inclusion and exclusion criteria and will be conducted at the Pain Outpatient Department (Schmerzambulanz) of the MHH.

At visit 1 (screening), written informed consent will be obtained. Subjects will undergo a physical examination and medical history taking. In- and exclusion criteria will be checked. Subjects will be familiarized with the floating tank. After this, the primary and secondary long-term outcomes will be assessed, as well as the expectancy/credibility rating.

At visits 2 - 6 (intervention), each separated by  $4 \pm 2$  days, in- and exclusion criteria will be checked again. Secondary short-term outcomes 1, 2 and 3 will be assessed. After this, a 5-minute ECG will be recorded for HRV analysis (short-term outcome 4). Subjects will then put on their bathing suits, take a shower and insert ear plugs before entering the floating tank (Tranquility, Floataway, Hingham, GB). The float itself will take 90 minutes. After the floating session subjects will leave the tank and take a shower to remove excess saline. Another 5-minute ECG will be recorded for HRV analysis (short-term outcome 4), before short-term outcomes 5 and 6 will be assessed.

After the last intervention, the subject is provided with a sealed envelope containing the questionnaires for the assessment of primary and secondary long-term outcomes and discharged.

On day 7 after visit no. 6 the subject is called by telephone and asked to fill out all questionnaires in the envelope and return it by mail.

This will be repeated at 12 weeks and 24 weeks after visit no. 6. Subjects in the intervention and control group will be unblinded after receipt of the last questionnaires.

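### Patients who stop floating early appear to be rated one week after their last attended float, nominally 4 to 16 days sooner than completers, and the sections that set the date are not reconciled

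*Combined protocol and SAP*

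**What the plan says.** The floats take place at visits 2 to 6, with 4 ± 2 days between visits (Study procedures on each study day). Three places set the date of the primary assessment:

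- **Endpoints** judges success "at first assessment (one week after the final floating session").
- **Study procedures on each study day** counts from the fifth float: "On day 7 after visit no. 6 the subject is called by telephone and asked to fill out all questionnaires in the envelope". For the follow-ups it adds: "This will be repeated at 12 weeks and 24 weeks after visit no. 6".
- **Data analysis** gives three conditions for the intention-to-treat analysis. The first excludes and replaces patients who leave before any float. The third excludes and replaces patients whose endpoint is missing. The second, between them, reads: "We will continue to acquire the endpoints, keeping the same time intervals, i.e. 1, 12 and 24 weeks after the last session". It does not say whether the last session is the last attended or the last scheduled.

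Two further statements bear on the point. Pain is rated by recall (Study assessments): "Ratings will assess the period of one week before the day of assessment". The questionnaires are handed over late (Study procedures): "After the last intervention, the subject is provided with a sealed envelope containing the questionnaires".

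**The concern.** An intention-to-treat comparison should measure every patient at a time that follows from the assigned schedule, not from what the patient did after randomisation. For completers the three sections agree. For a patient who stops after, say, the second float, they do not: visit 6 never happens, so the procedures section yields no date, while the Data analysis rule appears to yield a date one week after the second float. That patient's score describes pain part-way through the intended course, whereas a completer's describes pain after it.

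At stake is the primary test of intervention against control. If one arm loses more patients early, or loses them at a different stage, its mean assessment time after the first float moves relative to the other arm. Any change in pain over those days then enters the arm difference. The 12- and 24-week assessments move by the same number of days. There is also a practical question of whether an early stopper would have the questionnaires when they fall due.

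**Working it through.** The documents give no figure for the timing shift, so there is none to reproduce.

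**Which reading.** The second condition follows a rule for patients who leave before the first float and speaks of continuing to acquire endpoints. Its natural subject is the patient who stops after at least one float, and for that patient the last session is the last one attended. The alternative, a scheduled visit 6, has no defined date, because the spacing is flexible and no section says how to project it.

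**Timing under the natural reading.** Inputs from Study procedures: five floats, hence four gaps; gap *g* = 4 days, range 2 to 6; assessment 7 days after the anchor. With *k* floats attended, the assessment day counted from the first float is (*k* − 1)*g* + 7. The shortfall against a completer at the same pace is (5 − *k*)*g*.

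| Floats attended | Assessment day, nominal (range) | Sooner than completer, nominal (range) |
|---|---|---|
| 1 | 7 (7–7) | 16 (8–24) |
| 2 | 11 (9–13) | 12 (6–18) |
| 3 | 15 (11–19) | 8 (4–12) |
| 4 | 19 (13–25) | 4 (2–6) |
| 5 | 23 (15–31) | 0 |

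The 24-day extreme needs a stop after one float and a comparator whose gaps are all 6 days. Pace alone already spreads completers over 31 − 15 = 16 days.

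**Possible bias.** If all early stoppers stop after float 1, the shift in the arm difference is (difference in stopping proportion) × (difference in mean pain between the two times). Assume, purely for illustration, 4/25 stopping in one arm and 1/25 in the other:

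- Assumed pain difference of 5 to 15 points: 3/25 × 5 = 0.6; 3/25 × 15 = 1.8 points.
- Using instead the mean change in the untreated group of the cited exploratory study (Sample size calculation), 60.41 − 59.06 = 1.35 points: 3/25 × 1.35 = 0.16 points.
- Equal stopping in number and timing: 0 × any pain difference = 0.

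For scale, the planning difference is 24.50 + 1.35 = 25.85 points, so 0.6 to 1.8 points is 2% to 7% of it. With the planning SDs and 24 per group, the standard error is √[(35.58² + 24.67²)/24] = 8.8 points, so the same shift is about 0.07 to 0.2 standard errors.

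**Questionnaires.** If the envelope is handed over only after the fifth float, a patient who leaves a float expecting to return does not yet have it. The missed visit comes 2 to 6 days later (nominal 4), leaving 7 − 2 = 5 down to 7 − 6 = 1 days (nominal 3) to supply it before day 7. No section describes posting it.

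**The case against.** The strongest reply is that this is an ambiguity in wording. The Data analysis text does not say attended, its reference to unchanged intervals could point to the original schedule, and the other two sections assume the full course. Even on the attended reading the rule is defensible: everyone rates the seven days after their last float, so time since exposure is aligned, and the same rule applies in both floating arms. The first part stands to the extent that the attended reading remains an interpretation. It does not remove the problem, because the sections still give no agreed date for an early stopper. The second part also stands: the one-week recall is no special distortion for stoppers. But alignment on last exposure answers a different question from pain at the end of the assigned course.

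Some stronger readings are tempting and not supported:

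- A reader might infer that early stoppers are typically measured several weeks too soon. The nominal range is 4 to 16 days; 24 is the extreme.
- A reader might infer that the primary comparison is no longer protected by randomisation. That needs stopping that differs between arms together with pain that differs between the two times. The documents give no stopping rate, and nothing in them says the placebo float is less pleasant. Benefit lost by attending fewer floats belongs to the intention-to-treat effect and is not a timing artefact.
- A reader might infer that early stoppers certainly lack the questionnaires and are then removed as missing. This is inferred: if the last intervention is also read as the last attended one, they might receive the envelope. A patient removed as missing also contributes no mistimed score, so the two harms do not add up.

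One caution on the other side of the scale: 25.85 points is a difference against no treatment. The primary contrast is against a placebo float, and the Rationale expects large placebo effects, so the relevant difference may be smaller and the percentages above correspondingly larger.

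**Conclusion.** The point holds in a limited form. On its most natural reading, the plan ties an early stopper's primary and follow-up dates to when that patient stopped, which is a post-randomisation event, and it conflicts with the visit 6 anchor given elsewhere. The size in days follows from the plan's own schedule. The size in pain points does not: the 0.6 to 1.8 points rests on assumed stopping of 4/25 versus 1/25, all after the first float, and an assumed 5 to 15 point difference. The one relevant figure in the documents brings it down to 0.16. The risk to the primary result is therefore probably small, and about zero if stopping is alike in both arms. It merits a correction because the correction is cheap and makes the intention-to-treat dates independent of when patients stop, not because the trial's conclusion is shown to be at risk.

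**What to change.** - **Completers:** no change. Keep 7 days, 12 weeks and 24 weeks after their actual visit 6. Giving every patient one date set in advance would be a mistake: with visit 6 projected to day 16 and assessment on day 23, completers whose actual visit 6 fell anywhere from day 8 to day 24 would be rated from 15 days after their fifth float to one day before it.
- **Patients who stop after at least one float:** in Data analysis, replace the last-session anchor with 7 days, 12 weeks and 24 weeks after the date on which visit 6 would have taken place on the planned schedule, for example counting the remaining visits at the nominal 4-day spacing. The primary assessment then falls (*k* − 1)*g* + (5 − *k*) × 4 + 7 days after the first float. This is day 23 at the nominal pace for every *k*, and between day 17 and day 29 for any permitted pace (*k* = 4, *g* = 2 or 6), inside the completers' range of 15 to 31.
- **Consistency:** align the Endpoints and Study procedures sections with this rule.
- **Questionnaires:** hand over or post the envelope early enough that a patient who stops has it on the due date.

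The cost is a few sentences, an amendment to the ethics committee and some postage; the sample size does not change. The downside is that early stoppers are rated more than a week after their last float: (5 − *k*) × 4 + 7, that is 11 days after stopping at float 4 and up to 23 days after stopping at float 1.

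### The only planned robustness check is a per-protocol analysis, which cannot test the exclusion and replacement of patients without an endpoint in the main analysis

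*Combined protocol and SAP*

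**What the plan says.** All of this is in the Data analysis section unless stated otherwise.

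- **Primary test:** "The statistical test for the primary outcome will be a two-tailed two-sample t-test of the differences (before treatment - one week after treatment". Success is defined by that test alone: "The study will be positive if we observe a significant difference ( $p < 0.05$ ) between the intervention and the control group".
- **Main analysis set:** "All outcomes will be assessed in an Intention-to-Treat (ITT) analysis under the following conditions". Two of the conditions remove patients. One concerns early drop-out: "The subjects who drop out before the first session will be excluded from the analysis and replaced by other subjects". The other concerns absent outcome data: "In the case that we cannot assess the endpoint due to missing data, the subject will be excluded from the analysis and replaced by another". A third keeps follow-up going: "We will continue to acquire the endpoints, keeping the same time intervals, i.e. 1, 12 and 24 weeks after the last session". This appears to retain patients who stop floating early but still return their questionnaires.
- **Robustness:** "In order to test for the robustness of the therapeutic effect, we will also conduct per-protocol analyses afterwards". No other sensitivity analysis is planned. The ANCOVA and the non-parametric test replace the t-test under stated conditions; they are not additional checks.
- **Per-protocol membership:** not defined. The Endpoints section speaks of "a course of five successful floating sessions" without saying what makes a session successful. The sections on study procedures and on dietary and lifestyle restrictions give a visit spacing and a bar on new therapies, but neither is turned into a membership rule.

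**The concern.** A robustness check should vary an assumption on which the main result depends. The most exposed assumption here is that patients without a one-week pain score can be dropped and replaced without distorting the comparison. A per-protocol set, in the ordinary sense of the term, starts from the analysed patients and removes more of them. It therefore says nothing about those who were never in the analysis.

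It also adds a problem of its own. The patients it would mainly remove are those who stopped floating but supplied an endpoint, so randomised patients with observed outcomes are discarded because of what they did after allocation. The effect can move in either direction, depending on who stops and in which arm.

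At stake is the reading of the result. Agreement between the two analyses would be reported as robustness although the weakest assumption had not been examined. A more favourable per-protocol result could be selection alone.

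**Working it through.** **Inputs.** The sample size section gives changes of −24.50 ± 35.58 (n = 20) and 1.35 ± 24.67 (n = 17), Cohen's d of 0.83, and 25 recruited per arm for 24 needed. The documents give no rate of early stopping and no link between stopping and response, so both are assumed and shown as ranges.

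**1. The plan's own effect size.** Pooled SD = √[(19 × 35.58² + 16 × 24.67²)/35] = 31.07. d = (24.50 + 1.35)/31.07 = 0.83, which matches. An SD of 31 is used below.

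**2. What the check leaves untested.** The sets are nested: per-protocol within analysed within randomised. If m intervention patients are excluded alongside n = 25 analysed, and their true mean change is worse than that of the analysed patients by δ, the all-randomised mean is worse by δ × m/(n + m). Take δ = 24.50, meaning that the excluded patients did not change while the analysed patients improved as in the planning data:

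- m = 2: 24.50 × 2/27 = 1.8 points
- m = 4: 24.50 × 4/29 = 3.4 points

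Both m and δ are assumptions. No per-protocol result carries information on δ, because none of these patients is in either analysis.

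**3. Selective loss in the intervention arm only, true effect zero.** Remove the k of 25 patients who are lowest on a score that correlates ρ with improvement. The bias is ρ × SD × S/(25 − k), where S is the sum of the k largest expected order statistics of 25 standard normals (1.965, 1.524, 1.262, 1.066).

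| k (share) | ρ | Bias in points | Per-protocol rejection (simulated) |
|---|---|---|---|
| 2 (8%) | 0.3 | 0.3 × 31 × 3.489/23 = 1.4 | about 5.6% |
| 4 (16%) | 0.5 | 0.5 × 31 × 5.817/21 = 4.3 | about 7.7% |
| 4 (16%) | 0.7 | 0.7 × 31 × 5.817/21 = 6.0 | about 10.7% |

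The full set rejects in about 5% of trials. Repeat simulations gave 5.3% to 5.6% in the first row and 10.3% to 11.1% in the last.

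**4. The same loss placed elsewhere.**

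- *Control arm only:* the same sizes with the sign reversed.
- *Equal loss in both arms* (2 or 4 of 25, ρ = 0.5 to 0.7, zero effect): bias within 0.1 point, rejection about 5.4% to 6.6%.
- *One stopping threshold for both arms, floating effective at d = 0.83:* let patients stop when a score correlating 0.71 with improvement falls more than 1 SD below the control mean. Then 5.6% stop in the intervention arm and 15.9% in the control arm. The retained means rise by 0.71 × 0.120 = 0.085 SD and 0.71 × 0.288 = 0.204 SD. The apparent d is 0.83 + 0.085 − 0.204 = 0.71. Looser and stricter thresholds (1.5 and 0.5 SD) give 0.76 and 0.65. The effect shrinks.

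**5. How often the two verdicts agree under random exclusion.** Simulated with 25 per arm and exclusion in both arms:

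| Excluded per arm | d = 0 | d = 0.83 |
|---|---|---|
| 4% (1 of 25, the plan's allowance) | 98.2% | 95.3% |
| 20% | 95.7% | 86.2% |
| 40% | 93.9% | 73.1% |

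With 2 of 25 removed at random per arm, the estimates correlate √(23/25) = 0.96, yet the verdicts still differ in about 7% of trials at d = 0.83 and 9% to 10% at d = 0.6.

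**The case against.** The best defence has four parts.

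- **Success does not depend on it.** The per-protocol analysis cannot make the trial positive. The 5.6% to 10.7% is the rejection rate of a supporting analysis. This stands.
- **It answers a stated question.** The Endpoints section frames the long-term outcomes around "a course of five successful floating sessions", so an analysis of patients who completed the course has a purpose. This supports keeping it, though not as the robustness test.
- **The direction of bias is not given.** A reader might infer that per-protocol analysis favours floating because non-improvers stop. The documents do not support that. The comparator is a placebo float on the same schedule with patients blinded, so non-improvers may have the same reason to stop in both arms. Step 4 shows inflation, shrinkage or no bias, and with the plan's allowance of one patient the one-arm bias is only 0.3 to 0.7 × 31 × 1.965/24 = 0.8 to 1.8 points.
- **Agreement is not guaranteed.** A reader might also infer that the two analyses can hardly disagree. Step 5 shows that this depends on an exclusion rate the plan does not give.

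A further tempting reading is that membership would be chosen after the event by staff who know the arms. The text says only that the analyses are run afterwards. It does not say when membership is settled, and it is silent on whether the analyst is blinded.

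None of this answers the central point: no per-protocol set, however defined, tests the handling of patients without an endpoint.

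**Conclusion.** The concern holds in a limited form. The single planned robustness check cannot test the complete-case assumption of the main analysis, and it adds selection on behaviour after randomisation. That conclusion follows from the text and needs no assumed figure.

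The size of any distortion does rest on assumptions. It is about 1.4 to 6 points if 8% to 16% stop in the intervention arm only with correlations of 0.3 to 0.7, the reverse if the loss is in the control arm, and essentially nil if loss is equal. The primary test and its error rate are untouched. What should not be written, on this plan, is that the effect is robust because the per-protocol analysis agreed.

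**What to change.** Replace the robustness sentence with the following provisions.

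1. Robustness of the primary result is tested in all randomised patients in their assigned arm, including those whom the plan would exclude and replace. Missing one-week pain scores are multiply imputed from baseline pain and arm. Fixed no-change values are not enough, because single imputation understates the variance.
2. A delta adjustment then worsens the intervention arm's imputed values step by step until significance is lost, and the tipping value is reported. If only one or two scores are missing the tipping point may say little; it should be reported all the same.
3. The per-protocol analysis is supplementary and is not cited as evidence of robustness. Its membership rule, for example the number of sessions attended, is written down before outcomes are compared by arm.

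Baseline pain is taken at the screening visit, so no new data are needed. The cost is a change of SAP wording and one extra analysis. The downside is that the result may look less robust.
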